### Data management

All data from both arms of the trial will be entered and stored in the Peek database. Data will be transferred into Stata for analysis.

All field staff will undergo rigorous training in using Peek for screening and entering and recording data. Inter-observer agreement studies will be done for VA screening and refraction.

The Peek Acuity database will be password protected. At the end of the study, the data will be archived at LSHTM.

### Data analyses

Analysis will be in the groups to which children were randomly allocated. We expect all children will be given the spectacles required.

#### Primary outcome

The proportion of children wearing or having their spectacles with them at school at 3 to 4 months will be compared between the intervention and standard arms using the risk difference with 95% confidence intervals adjusted for cluster (school).

A separate analysis will also be undertaken to adjust for factors that may affect spectacle wear such as gender, age (linear term), degree of refractive error in the better seeing eye (linear term), previously wore spectacles (binary data), parental spectacle wear (binary data) and educational level (categorical data) if there are imbalances between the two arms of the trial. There will be no subgroup analysis.

In the Peek software the name of the school will never be entered, only the school study ID and the allocation code. The same applies to schools in the comparator arm. Schools will, therefore, only be identified by ID number while the data are being analysed.

Masked analysis of the primary outcome will be difficult as the database for schools allocated to the intervention arm will a larger number of fields than the comparator arm e.g., the SightSim image the child took home; the number and date of voice messages sent to parents.

#### Secondary outcomes

The proportion of children who access eye care after referral to Pushpagiri Eye Institute will be compared between arms, using the risk difference with 95% confidence intervals adjusted for cluster (school).

#### Other outcomes

Reasons for non-spectacle and spectacle wear will be compared between the two arms of the trial, after categorizing their responses.

Data on the cost per child wearing their spectacles at follow-up will only be analysed should the difference in spectacle wear be 20% or greater in the intervention arm.

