**Methods/Design:**

Cluster randomized, double-masked trial of children with and without uncorrected refractive errors or other eye conditions. Government schools in Hyderabad, India will be allocated to intervention (Peek) or comparator (standard programme) arms before vision screening. In the intervention arm Peek will be used for vision screening, SightSim images will be used in classroom teaching and will be taken home by children, and voice messages will be sent to parents of children requiring spectacles or referral.

In both arms the same criteria for recruitment, prescribing and dispensing spectacles will be used. After 3–4 months children dispensed spectacles will be followed up to assess spectacle wear, and uptake of referrals will be ascertained.

The cost of developing and delivering the Peek package will be assessed. The cost per child wearing their spectacles or accessing services will be compared.

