### Purpose

The purpose of this cluster randomized trial is to evaluate whether a health education package for teachers, parents and children (aged 11–15 years), delivered using Peek increases spectacle wear at 3 to 4 months and uptake of referral of children identified with other eye conditions.

The trial will also assess the cost of developing and delivering the Peek health education intervention and the cost of dispensing and delivering the spectacles in both arms of the trial. The cost per child wearing their spectacles at follow-up will be compared between the two arms of the trial.

The hypothesis is that the proportion of children wearing spectacles 3–4 months after they were given their spectacles is higher in schools allocated to the innovative Peek educational package than in schools randomized to the standard programme. The uptake of referrals is also anticipated to be higher in the schools allocated to the Peek educational package than those randomized to the standard programme.

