### Sample size calculation

A superiority margin of 20% was chosen to balance the anticipated higher costs of developing and delivering the Peek package. We estimate that we will need a study size of 450 children (225 in each arm) to detect a difference of 20% in spectacle wear between the intervention and comparator arm, assuming approximately 60% of children in the control arm will be wearing spectacles at follow-up, with a 95% confidence interval and 90% power. We have adjusted the sample size calculations for clustering using data from our previous study (unpublished) to estimate a design effect of 1.5. We have increased the sample size by 20% to allow for loss to follow-up. A total of 17,300 children will need to be screened to recruit 450 children for this trial. The communities are stable and few study children are expected to leave the school during the school year.

This will detect a 20% difference in spectacle wearing, determined using the sampsi command in Stata Statistical Software version 14 (StataCorp, College Station, TX, USA).

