### Other outcomes

At follow-up, each child not wearing their spectacles will be asked why they are not wearing them. Children wearing spectacles will be asked why they are wearing them. They will be asked if there is a second reason. Their response will be written down verbatim by field workers and coded afterwards, with reasons for non-wear likely to fall into the following categories: (1) never received them, (2) lost, (3) broken or scratched, do not like wearing them because (4) they were teased, or (5) appearance, or (6) headache or eye strain; (7) parents do not like the child to wear them, (8) did not notice an improvement in vision i.e. no benefit and (9) other, which will be specified.

The costs of developing the Peek education package, and for delivering both arms of the trial, will be determined using standard costing methods and data from Peek software developers. The cost per child wearing their spectacles at follow-up will be calculated and compared between arms.

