## Discussion

This trial is designed to evaluate whether a health education package for teachers, parents and children delivered using innovative mobile phone technology (Peek) increases spectacle wear at 3 to 4 months, as well as the uptake of referral of children identified during vision screening with other eye conditions. We will also assess the cost of developing and delivering the health education intervention in the intervention arm of the trial, and the cost of dispensing and delivering the spectacles in both arms of the trial. We will compare the cost per child wearing their spectacles at follow-up in both arms.

The Government of India recognizes the importance of correcting RE in children as they are included in the national programme for child health, called Rashtriya Bal Swasthya Karyakram (RBSK), and the National Program for the Control of Blindness. The health of schoolchildren is also recognized by international health experts, policy makers, governments and international agencies as contributing to child development, learning and socio-economic development. This includes FRESH (Focus Resources on Effective School Health) whose partners include Education International; Partnership for Child Development; UNESCO; UNICEF; the World Food Programme; the World Health Organization and the World Bank. Results of this project will, therefore, be of relevance to FRESH and local, national and international agencies.

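### The comparison of cost per child wearing spectacles is promised without condition in four places, but the analysis section runs it only if the wear difference is 20% or greater

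*Protocol article*

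**What the plan says.** Four places in the Protocol article commit to the comparison without any condition:

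- Abstract, Methods/Design: "The cost per child wearing their spectacles or accessing services will be compared".
- Purpose: "The cost per child wearing their spectacles at follow-up will be compared between the two arms of the trial".
- Other outcomes, where the outcomes are defined: "The cost per child wearing their spectacles at follow-up will be calculated and compared between arms". The same paragraph says that the costs of developing the package and of delivering both arms will be determined.
- Discussion: "We will compare the cost per child wearing their spectacles at follow-up in both arms".

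The Other outcomes paragraph under Data analyses sets a different rule. Data on cost per child wearing spectacles "will only be analysed should the difference in spectacle wear be 20% or greater in the intervention arm".

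The Sample size calculation gives the origin of the figure: "A superiority margin of 20% was chosen to balance the anticipated higher costs of developing and delivering the Peek package". The same 20% is the effect the trial is sized "to detect a difference of 20% in spectacle wear between the intervention and comparator arm". Control wear is taken there as about 60%.

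**The concern.** Both rules cannot hold. If wear differs by 15 points, Purpose requires the cost comparison and Data analyses forbids it. Both rules are stated in the article, so this is not a detail left to a fuller document.

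The threshold is also badly placed. It is the design difference itself, so an estimate centred on the planned effect falls below it about as often as above. A trial that clearly succeeds on its primary outcome could leave one of its stated purposes unanswered. When the comparison does run, it runs on an effect estimate selected for being high.

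**Working it through.** **Which 20%?** The sentence does not say absolute or relative, so reproduce the sample size first. The inputs, all from Sample size calculation, are 60% control wear, a 20% difference, a 95% confidence interval (read as two-sided 5%), 90% power, design effect 1.5 and 20% loss.

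- Taking 60% versus 80%, n = [1.96·√(2·0.7·0.3) + 1.2816·√(0.24 + 0.16)]² / 0.2² = 109 per arm, or 119 with the continuity correction.
- 119 × 1.5 = 178.5, and 178.5 / 0.8 = 223.1, so 224 per arm.
- The stated figure is 225 per arm. It reproduces within rounding with 20% as absolute points.

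**Chance that the condition is met.** Assume that it applies to the observed difference. With effective size m = analysed children per arm / 1.5,

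SE = √[(p_c(1 − p_c) + p_i(1 − p_i)) / m] and P(run) = 1 − Φ((0.20 − true difference) / SE).

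With 20% loss, 225 × 0.8 = 180 are analysed and m = 180 / 1.5 = 120. With no loss, m = 225 / 1.5 = 150.

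- 60% versus 80%, m = 120: SE = √(0.40 / 120) = 0.0577, P(run) = 0.50.
- 60% versus 75%, m = 120: SE = √(0.4275 / 120) = 0.0597, P(run) = 1 − Φ(0.05 / 0.0597) = 0.20.

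| True wear, control vs Peek | Runs (180 analysed) | Primary power (180) | Runs (225 analysed) |
|---|---|---|---|
| 60% vs 70% | 5% | 37% | 3% |
| 60% vs 75% | 20% | 70% | 17% |
| 60% vs 78% | 37% | 86% | 35% |
| 60% vs 80% | 50% | 93% | 50% |
| 60% vs 82% | 64% | 97% | 65% |
| 60% vs 85% | 82% | 99% | 84% |

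At a true 20 points, the 50% does not depend on sample size or design effect. By exact binomial, 47% to 48% of trials are suppressed, because a difference of exactly 20 points meets the condition.

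**Significant, but no comparison.** With control wear at 60%, the smallest significant observed difference is about 12 points (m = 120) or 11 points (m = 150). Every observed difference of 20 points or more is significant, so the share of trials that are significant yet get no comparison is power minus P(run). At 180 analysed this is 93% − 50% = 43% at 60% versus 80%, and 70% − 20% = 50% at 60% versus 75%.

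**Selection when it does run, at 60% versus 80%, m = 120.**

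- Mean estimate given that it is at least 0.20: 0.20 + 0.798 × 0.0577 = 0.246, an excess of 4.6 points.
- The excess splits in proportion to the variances, 0.24 : 0.16. Control wear averages 60 − 0.6 × 4.6 = 57.2% and Peek wear 80 + 0.4 × 4.6 = 81.8%.
- With costs per child fixed, the Peek-to-comparator ratio of cost per wearer is multiplied by (80 / 81.8) × (57.2 / 60) = 0.93, so it falls by about 7%.

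**If a confidence limit were meant.** Should the lower 95% limit have to reach 20 points, the comparison would be suppressed in about 97.5% of trials at a true 20 points.

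**The case against.** The strongest defence is that the condition is prespecified and has a stated reason. The authors judged 20 points to be the gain that would balance the package's extra cost, so a smaller gain makes cost per wearer moot; and a specific analysis section may be read as qualifying general statements of aim. The rationale does explain where the figure comes from. It does not reconcile the texts, since none of the four promises mentions a condition. It also presumes the answer: whether 12 or 15 points is worth the money is what the cost comparison is meant to show.

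Other parts of the defence stand. Cost is listed among the other outcomes and is absent from the stated hypotheses. The condition does not touch the primary estimate, its interval, the sample size or participant safety.

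A reader might infer three stronger things that the document does not support:

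- That the whole costing is suppressed. The outcome definition still has the costs of both arms determined; only cost per wearer is conditional.
- That the cost result is inflated by the full 24.6 against 20 points. That applies to an incremental cost per additional wearer, which the article does not plan. The planned measure is cost per wearer in each arm, where the ratio shifts by about 7%.
- That the rule is expressly about the point estimate. The sentence does not say. The observed-difference reading used here is the lenient one.

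**Conclusion.** The contradiction is plain on the page and needs no assumption. How often it would bite does rest on assumptions: 20% as absolute points (supported by the sample size) and the condition applied to the observed difference (inferred). Under these, about half of trials lose the comparison when the planned effect is exactly true. The figure of about 80% lost at 60% versus 75% further assumes the full 20% loss and a design effect of 1.5. The article expects few children to leave; with no loss the figure is about 83%, so the conclusion is not sensitive to this.

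The selection effect favours Peek but is modest for the planned measure. The point should be fixed because a named purpose may go unanswered in a positive trial. It does not threaten the primary result.

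**What to change.** In the Other outcomes paragraph under Data analyses, delete the 20% condition. State that cost per child wearing spectacles will be calculated and compared between arms, with its uncertainty, whatever the primary result. Keep 20 points only as a benchmark for interpreting that result.

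The minimum alternative is to write the condition into the Abstract, Purpose, outcome definition and Discussion, and to say whether it refers to the estimate or a confidence limit. That makes the text consistent, but a purpose of the trial could still go unanswered.

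The preferred change costs one sentence and a little more analysis work. It needs no new data, because the costs of both arms are already to be determined.

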### Data monitoring

A data monitoring committee will not be required. There is no reason to expect significant adverse effects. Interim analyses are not planned.

### Harms

Neither arm of the trial has any anticipated harms. If spectacles are prescribed inaccurately, or fitted incorrectly, they can cause blurred vision and/or eyestrain or headaches whilst using the spectacles. In this trial all refractions and spectacle fittings will be undertaken by highly experienced optometrists to ensure inaccurate prescribing is unlikely. When children are followed up at 3–4 months, they will be asked whether these symptoms were the reason they did not wear their spectacles. If a child reports any of these symptoms, they will be refracted again and given new spectacles if required.

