**Fig. 1 Fig1:**
[figure not shown]
Study flowchart

To standardize data recording, data will be entered using dedicated Peek software in both arms of the trial. The software will have range and consistency checks built in. Field workers and optometrists working in schools in both arms of the trial will be given tablets for data entry, and data will be regularly backed up onto a cloud server. In both arms of the trial the head teacher will be given a list of all the children in their school who require spectacles or referral. Classroom teachers will also be given a list of children in their class who require spectacles or referral.

The following information will be collected by trained field workers by interviewing all eligible children in both arms of the trial: name, age, gender, class and date of birth; parents’ mobile phone number, language used in the home; parental education; occupation of parents; whether one or both parents wear spectacles for distance vision and limited information on household assets taken from National Household Survey questionnaires. Data on subjective refraction and best-corrected VA in each eye will be recorded as well as the prescription of the spectacles required and the frame the child selected from a selection of thirteen plastic frames of different colours. In the intervention arm, the SightSim image the child selects to take home will be recorded.

In both groups of schools, only children with significant REs will be prescribed spectacles i.e., where after correction, the acuity improves by two or more lines binocularly. Children will select the frames they prefer from a range of coloured plastic frames. Each pair of spectacles will have a unique code. Spectacles will be delivered to the schools by field workers at no cost as soon as possible and all children in each school will receive their spectacles on the same day. At the school, field workers will double-check the name of each child against the lists given to classroom teachers, to ensure that each child receives the correct spectacles. The field workers will measure children’s VA with their new spectacles.

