### Primary outcome

The primary outcome is defined as the proportion of children who are wearing their spectacles at an unannounced visit to the school 3 to 4 months after delivery of the spectacles. A new field worker will be recruited and trained to collect the primary outcome data who will be masked to the hypothesis and intervention arm. Spectacle wear will be ascertained using the four categories defined by Wedner [18] where categories 1 or 2 below define spectacle wearing, and categories 3 or 4 as non-spectacle wearing: (1) wearing the spectacles at the time of the unannounced visit, (2) not wearing the spectacles at the time of the visit but have them at school, (3) not wearing the spectacles at the time of the visit but said they are at home, and (4) not wearing the spectacles at the time of the visit as they are broken or lost.

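### Symptoms from the spectacles are asked about only as a reason for not wearing them, so children who wear them are never prompted, and the share asked falls as wear rises

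*Protocol article*

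**What the plan says.** The Harms section of the protocol article names the possible harm of a wrong prescription or poor fit: "they can cause blurred vision and/or eyestrain or headaches whilst using the spectacles". It then states how this will be picked up at the 3–4 month visit: "they will be asked whether these symptoms were the reason they did not wear their spectacles". The response follows: "If a child reports any of these symptoms, they will be refracted again and given new spectacles if required".

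The Other outcomes section under Methods/design gives the matching questions. For non-wearers, "each child not wearing their spectacles will be asked why they are not wearing them", with "6) headache or eye strain" as one of the expected codes. For wearers, "Children wearing spectacles will be asked why they are wearing them". No symptom question to wearers is described.

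The Primary outcome section sorts children into four groups, where "categories 1 or 2 below define spectacle wearing, and categories 3 or 4 as non-spectacle wearing". Category 2 covers children who have the spectacles at school but not on.

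The only other stated check with the spectacles on is at delivery, in the section on identification and recruitment: "The field workers will measure children’s VA with their new spectacles".

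The Other outcomes paragraph under Data analyses says that reasons for wear and non-wear will be compared between arms. It fixes no denominator.

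**The concern.** The harm is described as something that happens in use, but the question presupposes that the child did not use the spectacles. The children most exposed to an inaccurate lens or poor fit are those wearing them, and they are asked only for their reasons for wearing. A wearer with headaches is identified only if the child raises it unprompted.

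The second problem is between arms. Being asked depends on whether the child is wearing the spectacles, which is close to the primary outcome and is expected to differ by arm. If Peek raises wear, fewer Peek children are asked. Any symptom count over all children would then be lower in that arm for a reason unrelated to symptoms.

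**Working it through.** **Planning figures.** The plan gives no figure for harms, so the illustration uses the inputs of its Sample size calculation: 60% wear in the comparator, a 20-point difference (80% with Peek), 95% confidence, 90% power, design effect 1.5, 20% loss, 225 per arm.

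The stated size reproduces closely:

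- Uncorrected n = [1.96·√(2·0.7·0.3) + 1.2816·√(0.6·0.4 + 0.8·0.2)]² / 0.2² = 108.2.
- With continuity correction, n = (108.2/4)·[1 + √(1 + 4/(108.2·0.2))]² = 118.0, or 119 after rounding up at each step.
- 119 × 1.5 = 178.5, and 178.5 / 0.80 = 223.1, so 224 per arm against the stated 225.
- Expected at follow-up: 225 × 0.80 = 180 per arm.

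**Who is asked.** Let w be the share wearing. If every outcome wearer goes unasked, the share asked is 1 − w.

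| | Comparator | Peek |
|---|---|---|
| w | 60% | 80% |
| Not asked, of 180 | 108 | 144 |
| Asked, of 180 | 72 | 36 |

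Together 108 + 144 = 252 of 360 (70%) are not asked. This is an upper bound.

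**Category 2.** These children count as wearers for the outcome, but because they do not have the spectacles on they may be asked why not. Let q be the share of outcome wearers in category 2; the documents do not give it. The unasked share is then w(1 − q). At q = 0 it is 60% and 80%. At an assumed q = 0.5 in both arms it is 30% and 40%, or 54 + 72 = 126 of 360 (35%), and the shares asked are 70% and 60%. Category 1 children, who have the spectacles on, are unasked at any q.

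**Effect on counts.** The symptom rate r is not in the documents. Assume that it is equal in both arms and unrelated to wear, with q = 0. Captured cases are 180·r·(1 − w) and missed cases are 180·r·w.

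| r | Captured, comparator vs Peek | Missed, comparator vs Peek |
|---|---|---|
| 2% | 1.44 vs 0.72 | 2.16 vs 2.88 |
| 5% | 3.6 vs 1.8 | 5.4 vs 7.2 |
| 10% | 7.2 vs 3.6 | 10.8 vs 14.4 |
| 20% | 14.4 vs 7.2 | 21.6 vs 28.8 |

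Over all children, the captured ratio (Peek/comparator) is 0.20/0.40 = 0.5 at any r. At q = 0.5 it is 0.60/0.70 = 0.86. Among non-wearers only, with q = 0, each arm shows r and the artefact disappears, but nothing is learned about wearers.

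**If symptoms drive non-wear.** Assume, for illustration, 5% in wearers and 20% in non-wearers in both arms (q = 0).

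- Comparator: true rate 0.6·5% + 0.4·20% = 11%, captured 8%, so 3/11 = 27% of cases missed.
- Peek: true rate 0.8·5% + 0.2·20% = 8%, captured 4%, so 4/8 = 50% missed.

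The share missed falls from 60% and 80% to 27% and 50%. The direction stays: the captured ratio is 0.5 against a true ratio of 8/11 = 0.73.

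**The case against.** - **No symptom comparison is planned.** The Harms section uses the question to trigger another refraction, and the analysis section compares reasons for wear and non-wear. Summarised among non-wearers, equal rates would look equal. This stands: the halving needs an all-children denominator that the plan does not fix. It does not help the wearers, about whom the plan would still have no elicited information, and a comparison restricted to non-wearers conditions on a group formed after randomization.
- **The protocol does not break its own harm rule.** A reader might infer that it does. The rule is conditional on a report and is not limited to non-wearers, so a wearer who volunteers symptoms is covered. There is no contradiction; the rule simply depends on spontaneous reports in that group.
- **The 70% is too high.** A reader might take 252 of 360 as the number never asked. The treatment of category 2 makes it a ceiling, and the documents do not allow the true figure to be calculated.
- **Acuity is checked at delivery.** This may catch gross errors in both arms, but it precedes any period of use and does not ask about headache or eyestrain.
- **The article is condensed and the follow-up form may ask more.** That is possible. But the point does not rest on silence: two sections state who is asked what, and they agree.
- **The harms are mild and the spectacles are supplied in the same way in both arms.** This is correct, and it limits the importance of the point.

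**Conclusion.** The point holds as a weakness in how symptoms are ascertained. As written, blur, eyestrain and headache are elicited only as reasons for non-wear, so in children wearing their spectacles they are found only if volunteered. The share of children asked falls as wear rises, and symptom counts over all children would not be comparable between arms if wear differs.

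The size can only be illustrated. Up to 60% of comparator and 80% of Peek children would go unasked at the planned wear, and the captured rate with Peek would be half the comparator's. The halving assumes that the planned wear rates occur, that category 2 children are not asked, that true symptom rates are equal and unrelated to wear, and that all children form the denominator. The documents do not support the stronger inference that the trial will report a spurious halving of symptoms, since neither a symptom rate nor such an analysis is given.

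A lesser point in the same text is that Harms describes a direct question on symptoms, while Other outcomes describes open answers coded afterwards. Blur is named as a harm but has no code under that name.

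This is a cheap improvement to safety ascertainment. The primary outcome and the sample size are not affected.

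**What to change.** Ask every child seen at follow-up, whatever the wear status, the same closed question on blur, headache and eyestrain when using the spectacles. Allow an answer for children who have not used them, and put the question after wear status has been recorded so that it cannot influence the primary outcome. Report the answers by arm over all children followed up. Keep the open question on reasons for wear and non-wear as a separate item, and align the Harms and Other outcomes sections on the wording, including whether blur is recorded. Leave the response to a positive answer as the Harms section states it.

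The cost is one extra question at a visit already planned, and a few more children seen again under the existing rule.
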